
### Participant timeline {13}

Figure 1 shows how enrolment, interventions, and study assessment will flow over an approximate period of 24 months.

**Fig. 1 Fig1:**
[figure not shown]
Schematic of trial enrolment, interventions, and assessments. Abbreviations: SP standardized patient; SPI standardized patient instructor

### Sample size {14}

We used the exemplary dataset method in SAS to assess the power for a difference-in-difference analysis for a binary primary outcome (whether spinal imaging is ordered or not) that is assumed to have a 25% incidence in the control condition and that the effect of the intervention would be to lower the incidence by 7 percentage points. Based on empirical analysis of related data, we assumed that the outcome would have residual within-clinic and within-clinic/within-doctor correlations of 1% and 4%, respectively. We assumed hypothesis testing would be 2-tailed, with the type-1 error controlled at 5%. With 8 clinics 6 clinicians per clinic, and 92 patients per doctor (57 pre-intervention and 35 post-intervention), we would have 80.1% power to detect the effect of interest. To retain the desired sample size of 48 clinicians, we will seek to recruit at least 55 for participation.

### Recruitment {15}

We will recruit RCT clinicians during medical staff meetings (either in-person or online) and via follow-up email. During recruitment, we will inform physicians that the study will assess aspects of doctor communication but will not inform them of study hypotheses or the specific focus on spinal imaging. Similar recruitment strategies resulted in high participation rates in our previous SPI or observational studies [19, 21, 26].

## Assignment of interventions: allocation

### Sequence generation {16a}

We will stratify randomization by health system (UC Davis vs. Sutter) and primary vs. urgent care (within the Sutter system only). We will then use block randomization (in blocks of four clinicians) to ensure balance by overall, by health system, and by primary vs. urgent care.

### Implementation {16c}

The study statistician will stratify randomization by participating health system and by primary vs. urgent care status. Within each stratum, permuted block randomization will be used.

## Assignment of interventions: blinding

### Who will be blinded {17a}

It will not be feasible to blind study clinicians to intervention and control assignments. Although we will not explicitly inform control clinicians of their assignment, these clinicians may infer their assignment as they will receive no standardized patient instructor visits.

We will blind research assistants hired to code transcripts of recorded follow-up visits with standardized patients. We will attempt to recruit standardized patients solely for the 9-month evaluation visits so that these standardized patients, who will rate clinicians on non-verbal communication, can be blinded to intervention vs. control arm. To blind coders, the project coordinator will assign a study identification number to each transcript prior to distribution to coders. The coordinator will also review the transcript for any language that may divulge the intervention assignment and will delete this from the transcript. To blind standardized patients, the project coordinator will not divulge to the standardized patients the intervention assignment of clinicians.

We will blind the study statistician to intervention assignments. The data analysts who extract diagnostic testing data from EMR databases will be blinded to intervention status. These data will be securely transferred to a project data analyst who will construct the final analytic dataset. The project data analyst will not be blinded to allocation assignments and will assign an unlabeled indicator variable to each clinic, thereby masking the intervention assignment. The final analytic dataset will be transmitted to the study statistician, and the data analyst will only divulge allocations after the study statistician has completed planned primary and secondary analyses.

### Procedure for unblinding if needed {17b}

We do not anticipate any circumstance under which the research assistants or the study statistician will need to be unblinded.

## Data collection and management

### Plans for assessment and collection of outcomes {18a}

Data for the primary outcome (spinal imaging rates) and secondary outcomes related to diagnostic testing (neck imaging, other diagnostic testing) will be derived from electronic medical record data for enrolled clinicians for the 24-month period prior to randomization and up to 18 months after the final SPI visit (or after enrollment for control clinicians). Information technology staff at the two health care systems will extract aggregate datafiles containing the required data on procedure and diagnostic codes, orders entry, and testing completion. These data will be transmitted to the study data analyst, who will develop analytic variables and a complete analytic dataset.

For the secondary outcome of clinician use of targeted communication techniques, we will use data from coded transcripts of standardized patient follow-up visits and standardized patient ratings of clinician use of non-verbal behaviors. The research assistants will be trained and supervised by a medical sociologist ([name]). Each transcript will be coded twice by blinded research assistants with disagreement resolved by consensus or the medical sociologist. Final coding results and standardized patient ratings of non-verbal behaviors will be double entered into a Research Electronic Data Capture (REDCap) database, and at study end, these data will be transmitted to the data analyst for linkage into the analytic dataset.

Baseline and follow-up clinician surveys will be collected using REDCap surveys that clinicians will complete using an emailed weblink.

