### Intervention description {11a}

Clinicians randomized to the control group will receive no intervention during the trial period.

Clinicians randomized to the intervention group will receive three visits over a 3- to 6-month period with an SPI scheduled during normal clinic hours for 20-min in-person office visits. (Due to the COVID-19 pandemic, clinicians may opt to have the second or third SPI visits as video visits, although we will require that the initial SPI visit be conducted in-person.) Clinicians will be aware that they are scheduled to see a standardized patient, and the SPI will begin the visit by reminding the clinician that they are an SP and orienting the clinician to the overall visit plan. During each visit, SPIs will spend 10–12 min portraying a patient with acute back pain based on pre-specified role profiles. During this time, SPIs will assess clinicians’ performance on a three-step intervention model for communicating a watchful waiting message regarding spinal imaging that is based on psychological theory [15–17], extant literature and preliminary studies [18–22], key informant interviews with clinicians, and focus groups with patients (Table 1). We consider the model to be preliminary at this stage, as we may modify content based on additional key informant interviews or our experience during SPI training and intervention pilot testing.

**Table 1 Tab1:** Watchful Waiting to Avoid Inappropriate Testing (WAIT): intervention model with key skills and criteria for fulfillment

Step	Key skills	Criteria for fulfillment with examples (to guide intervention content and coding)
1. Set the stage for deferred imaging by building trust	1. Demonstrate openness and interest 2. Avoid interruptions 3. Identify the patient’s motivating concern or expectations	1. Non-verbal openness and engagement • Sits, orients toward the patient • Maintains open body position, leans in • Frequent, attentive eye contact • Engaged facial expressions or gestures (e.g., nodding) 2. Clinician does not interrupt early on. Allows patient to “tell their story” without cutting them off. 3. Clinician probes or asks for more information when patient signals a major underlying or motivating concern or expectations: “It sounds like you are worried that you seriously injured your back. Is that right?” or “You seem to be concerned that you need an MRI. Can you tell me more about that?”

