The post-intervention rate of cervical spinal imaging among adults adjusted for baseline rate (to examine the potential for the intervention effects to generalize beyond the management of low back pain (objective 3)). We will compute this analogously to the rate of lumbar spinal imaging but only among patients with “neck pain” diagnoses in the primary position using ICD-9 and ICD-10 codes [23, 24].The rate of overall diagnostic testing among adult patients adjusted for baseline. For these analyses, we will identify counts of diagnostic tests ordered during primary care visits participating clinicians during the 24-month period prior to their first SPI visits and from the date of their final SPI visits through up to 18 months, consistent with our pilot trial [21]. Specifically, we will include visit-level counts of the following diagnostic test categories: hematology and chemistry, urine and body fluid analyses, microbiology, imaging tests (subcategorized as non-spine plain x-ray or sonography, spinal x-ray, non-spine MRI or CT, neuroimaging), electrocardiography, other cardiac tests, and miscellaneous tests (e.g., nuclear medicine). We will exclude tests performed for screening or prevention (e.g., lipid or diabetes mellitus tests, bilateral screening mammograms). Both UC Davis and Sutter utilize the same EMR system (Epic), and so we expect to be able to harmonize patient and visit EMR data extracted from the two systems. The analysts compiling these data will be blinded to the study arm.The post-intervention rate of test *ordering* which is distinct from test *completion*. These outcomes will be computed similarly as the test completion outcomes specified above, but we will use a signifier in the electronic medical record that a given test was ordered by the clinician. Because not all ordered tests are completed by patients, we assess test ordering as a secondary outcome.Approximately 7–9 months after clinician enrolment (and after all intervention visits are completed among intervention physicians), intervention and control physicians will receive a visit by a single non-instructor SP portraying a patient with acute low back pain. Using SP observations and audio-recordings of these visits, we will ascertain as a *secondary outcome* the extent to which clinicians implemented various steps of the model. We will use iterative systematic content analysis of transcripts from audio-recorded visits to quantify how frequently clinicians engaged in the specific steps emphasized in the intervention, as well as the overall extent to which clinicians implemented watchful waiting. To guide coding, we will develop a manual to guide trained research assistants in coding transcriptions while simultaneously listening to audio-recorded visits. As the first step in the model addresses non-verbal communication, we will also incorporate standardized patient ratings on non-verbal communication. Coders will be blinded to clinician allocation. To the extent possible, we will blind SPs to the intervention group, but given the small number of total SPs, some SPs may revisit clinics where they previously performed the role of intervention SPIs, thereby making SP blinding difficult if not impossible without training and hiring entirely new SPs for the assessment phase. Inter-observer agreement for coding targeted behaviors will be assessed using Cohen’s kappa, and disagreements will be resolved by consensus or by review of the audio-recording by a third party. We have successfully used this process to assess physician-patient interaction in other studies [19, 21]. Ultimately, this process will generate a summary scale expressing the extent to which clinicians engaged in intervention steps during SP visits.Six months after final SPI visits, we will survey randomized clinicians regarding the use of watchful waiting when actual back pain patients request low-value spinal imaging. We will also survey physicians regarding the use of watchful waiting for neck pain, other regional musculoskeletal pain syndromes (e.g., shoulder and knee pain), and in other contexts (e.g., when patients request antibiotics). For intervention clinicians, the survey will also inquire regarding clinicians’ views on the quality, acceptability, and utility of the SPI training. Clinician self-reported use of watchful waiting during the follow-up period will constitute a *secondary outcome* of the trial.To address concerns that a watchful waiting strategy might undermine patient trust and confidence in physicians, we will assess as a *secondary outcome* for potential adverse impacts of the intervention on patient experience. To develop this measure, we will link study physicians to pre- and post-intervention patient experience data collected by the health systems as part of routine care. We have confirmed the feasibility of such linkage with UC Davis executives and are exploring this possibility within the Sutter system. These measures include visit-level Consumer Assessment of Healthcare Providers and Systems (CAHPS) results [25], which we will use to develop pre- and post-intervention summary measures of patient experience. Analyses will assess for adjusted differences in post-intervention patient experience measures among intervention physicians as compared to control physicians, after adjustment for baseline patient experience.

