### Plans to promote participant retention and complete follow-up {18b}

Clinician retention will be encouraged by the payment of a $100 gift card and $125 of Relative Value Unit credit for each standardized patient visit as a means of compensating clinicians for lost productivity. We will offer clinicians in the control arm the opportunity to receive a single SPI visit after completion of data collection. Utilization data for clinicians who drop-out of the study will be analyzed when available, according to the assigned study arm.

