## Trial status

This protocol is dated October 9, 2020. Recruitment of clinicians and clinics began on November 4, 2020, and is anticipated to continue through May 31, 2021.

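### Follow-up for the primary outcome opens at the final SPI visit in the intervention arm but at enrollment in the control arm, so the post-period is offset by arm and undefined for clinicians with no SPI visit

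*Protocol article*

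**What the plan says.** - **Follow-up window.** Plans for assessment and collection of outcomes {18a} takes electronic record data for the 24 months before randomization and then for "up to 18 months after the final SPI visit (or after enrollment for control clinicians". This is the only place that gives controls a start date. Outcomes {12} and Statistical methods {20a} speak only of a post-intervention period.
- **Length of training.** Under Intervention description {11a}, intervention clinicians "will receive three visits over a 3- to 6-month period with an SPI". Outcomes {12} puts the follow-up standardized patient visit about 7 to 9 months after enrolment, once all training visits are done.
- **Primary test.** Statistical methods {20a} tests the interaction between arm and a pre/post indicator in a Poisson mixed model. The only further fixed effects named are baseline clinician characteristics.
- **Intention to treat.** Sections {11b} and {20a} analyze clinicians as allocated. Section {18b} adds: "Utilization data for clinicians who drop-out of the study will be analyzed when available, according to the assigned study arm".
- **Calendar setting.** Under Trial status, recruitment "began on November 4, 2020, and is anticipated to continue through May 31, 2021". Trial design {8} describes rolling enrollment during the pandemic, and Outcomes {12} notes that telemedicine had grown.
- **Other anchors.** For the secondary overall-testing outcome, Outcomes {12} counts tests "during the 24-month period prior to their first SPI visits and from the date of their final SPI visits through up to 18 months". The clinician survey is timed at six months after the final SPI visits.

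**The concern.** A pre/post-by-arm interaction removes a time trend shared by both arms when the post-period sits at the same place in time in each. Here it does not. A control contributes months 0 to 18 after enrollment; an intervention clinician contributes about months 3 to 21, up to months 6 to 24. Controls supply the earliest months after enrollment and intervention clinicians do not. Allocation itself creates the offset, so neither randomization nor the stratified blocks can balance it, and more clinicians would not reduce it.

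The second problem is that the start date in one arm depends on what happens after randomization. Slow completers get later windows. A clinician who stops after one visit has an ambiguous start date, and one who receives no visit has none. The protocol says such clinicians' data will be used in their assigned arm but not over which months, so the intention-to-treat analysis of the primary outcome cannot be carried out for them as written.

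**Working it through.** **Inputs from Sample size {14}.** Imaging is "assumed to have a 25% incidence in the control condition", and the intervention is expected to "lower the incidence by 7 percentage points", that is, from 25% to 18%. There are 48 clinicians (24 per arm), each with 57 pre and 35 post patients. Correlations are 1% (clinic) and 4% (clinician within clinic), 5% in total. The test is two-sided at 5% and the stated power is 80.1%.

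**Step 1: reproduce the stated power.** Clinic and clinician intercepts cancel in the pre/post contrast. On the logit scale:

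- Variance = [2/(57 × 0.25 × 0.75) + 1/(35 × 0.25 × 0.75) + 1/(35 × 0.18 × 0.82)]/24 = (0.1871 + 0.1524 + 0.1936)/24 = 0.0222, so SE = 0.149.
- Effect = logit(0.25) − logit(0.18) = 0.418, and 0.418/0.149 = 2.80.
- Power = Φ(2.80 − 1.96) = 80.0%, against 80.1% stated. The power figure is sound and is not at issue.

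**Step 2: standard error under the null, in percentage points.**

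SE = √[2 × 0.25 × 0.75 × (1 − 0.05) × (1/57 + 1/35)/24] = √0.000685 = 0.0262, or 2.62 points.

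**Step 3: offset and overlap.** For same-day enrollees with a lag of L months, the overlap is (18 − L)/18: 15/18 = 83% at 3 months and 12/18 = 67% at 6 months. This takes the span of the visits as the lag. The time from enrollment to the first visit is not stated and would add to it. The follow-up visit at 7 to 9 months, after all training, is the outer limit the document implies.

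**Step 4: bias from a steady drift.** Bias = drift per year × L/12. The rejection rate under a true null is P(|Z + bias/2.62| > 1.96). The drift is assumed, because the documents give none.

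| Assumed drift (points/year) | Bias at 3 months | Bias at 6 months | Share of 7 points | Type I error |
|---|---|---|---|---|
| 0 | 0 | 0 | 0% | 5.0% |
| 1 | 0.25 | 0.50 | 4–7% | 5.1–5.4% |
| 2 | 0.50 | 1.00 | 7–14% | 5.4–6.7% |
| 3 | 0.75 | 1.50 | 11–21% | 5.9–8.8% |
| 6 | 1.50 | 3.00 | 21–43% | 8.8–20.9% |

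The sign follows the trend. If imaging rises over time, the later intervention window hides part of a real effect; if it falls, the intervention looks better than it is.

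**Step 5: bias from a temporary shock.** If the imaging rate shifts only during the first L months after enrollment, only controls contribute those months, and bias = shift × L/18. A 5-point shift gives 5 × 3/18 = 0.8 to 5 × 6/18 = 1.7 points. A 10-point shift gives 1.7 to 3.3 points.

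**Step 6: with a common window.** L = 0, so the bias from a shared trend is 0. Power stays about 80% provided 35 post-period patients per clinician still accrue.

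**The case against.** The strongest reply is that the problem is modest and of unknown sign. Most of it stands as a limit on size.

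- A reader might infer that the arms are compared over separate calendar periods, or that the contrast absorbs the whole secular trend. The documents do not support that. The windows share 67% to 83% of their length, blocks of four keep enrollment dates similar across arms, and only the part of a trend inside the offset enters.
- Equal windows are not the only route to an unbiased contrast. No trend, or a properly modelled one, would also do. A separate analysis plan, not shown here, could add a calendar-time term. That would not give a start date to a clinician with no SPI visit, and the arm-specific window is fixed in the protocol itself.
- The drift range has no source in the documents. Their only remark on trend, in Background and rationale {6a}, is that an awareness campaign had not reduced early imaging. That suggests little movement, though before the pandemic. At 1 point per year the effect is negligible, and the 43% and 21% figures need 6 points per year and a 6-month lag for every clinician.
- A reader might also infer that the primary outcome's baseline differs by arm. It does not: {12} and {18a} give 24 months before randomization. The first-SPI-visit anchor belongs to the secondary overall-testing outcome.
- The phrase up to 18 months could mean a common data cut. That would align the ends of the windows, leave the starts different and give controls longer follow-up.
- The timeline figure is not shown and cannot be checked for where control follow-up is placed.

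**Conclusion.** The point holds. As written, the primary contrast carries an arm-dependent time offset of roughly 3 to 6 months or more, no named term removes it, and one arm's start date is a post-randomization event that some clinicians may never reach. The undefined window rests on no assumption about trend.

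The size of the bias does rest on one. Over assumed drifts of 0 to 6 points per year it is 0 to 3.0 points, with a type I error of 5% to about 21% under the design's own variance inputs. It matters from about 3 points per year, or with a shock in the months just after enrollment. The direction cannot be stated. The documents do not show that a bias of this size exists, only that the plan leaves the primary result open to it.

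**What to change.** 1. Define the primary post-period as the same interval since randomization for every clinician in both arms, whatever SPI visits were completed; for example, opening when training is scheduled to be finished and lasting 18 months. Envelopes are opened at enrollment, so the two dates should coincide.
2. Keep the 24-month pre-randomization baseline.
3. Add a calendar-time term to the primary model. Rolling enrollment and overlapping windows make it estimable.
4. Keep the visit-anchored window as a sensitivity analysis, giving each control the elapsed time of a matched intervention clinician.
5. Separately, anchor the overall-testing windows and the clinician survey to randomization as well, because controls have no SPI visits during follow-up.

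The cost is protocol wording and extraction dates, settled before data are extracted. Control data would run later than month 18, but if the window opened at month 6 it would close at month 24, which an intervention clinician finishing at month 6 already requires (6 + 18 = 24). Fast completers' early post-training visits drop out of the primary analysis, and slow completers' not-yet-trained visits may slightly dilute the effect. The sample size need not change if 35 post-period patients per clinician accrue.

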### Plans to promote participant retention and complete follow-up {18b}

Clinician retention will be encouraged by the payment of a $100 gift card and $125 of Relative Value Unit credit for each standardized patient visit as a means of compensating clinicians for lost productivity. We will offer clinicians in the control arm the opportunity to receive a single SPI visit after completion of data collection. Utilization data for clinicians who drop-out of the study will be analyzed when available, according to the assigned study arm.

